**3) Summary**

Inpatient treatment for complicated severe acute malnutrition (SAM) continues to have a high mortality in Africa. This is partly because children are commonly brought for admission because they are seriously ill, rather than being brought to hospital because of malnutrition alone. Mortality rates are especially high where SAM is complicated by HIV or TB. The early phase of inpatient nutritional treatment for severe acute malnutrition is based on a low-protein milk known as F75, which is given to improve metabolic homeostasis prior to the re-feeding to achieve catch-up growth. F75 provides a high proportion of energy from carbohydrates, including sucrose, lactose and maltodextrin. However, malabsorption of different types of carbohydrates, but lactose in particular, is known to occur in SAM and may lead to osmotic diarrhoea. Diarrhoea is common in children with SAM and is associated with increased mortality. Furthermore, switching from a catabolic state to a high energy diet that consists of predominantly carbohydrates can lead to ‘re-feeding syndrome’ that may lead to severe electrolyte abnormalities and multiple organ dysfunction.

The aim of this trial is to determine whether reducing the carbohydrate content of F75, and removing lactose, improves the stabilisation of severely malnourished children. The trial will involve randomising children who are eligible to receive F75 milk to either the current formulation or a revised formulation. Both formulations will be given according to current recommendations regarding frequency of feeding and caloric value. Since the purpose of F75 is to stabilise the child metabolically and biochemically, the primary endpoint of the trial will be time to stabilisation (the end of the first phase of treatment for severe acute malnutrition). Blood and stool samples at admission and after three days will be used to determine the effects on carbohydrate and fat malabsorption and evidence of the re-feeding syndrome. Children will be followed up until discharge from hospital. The project has been planned in consultation with the World Health Organisation (WHO) and, if the revised formulation of F75 results in improved outcomes, will lead to a global change in recommendations for its formulation.

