**4) Introduction**

Admission to hospital with complicated severe acute malnutrition (SAM) in Africa commonly has a case fatality of 10-30%.[^1-3^](#_ENREF_1) Importantly, children are usually admitted to hospital because they are severely ill rather than for malnutrition alone. Mortality may be improved to some extent by adherence to WHO recommended management,[^1^](#_ENREF_1)^,^[^2^](#_ENREF_2) but the direct application of these guidelines to all contexts is controversial.[^4^](#_ENREF_4) The WHO guidelines were designed on the basis of historical data on nutrient requirements and medical treatments and almost none of the recommendations are supported by evidence from clinical trials.

For the treatment of complicated inpatient SAM, the guidelines consist of three distinct phases of treatment:[^5^](#_ENREF_5) phase 1 or stabilization phase where a low protein, liquid diet (F75) is introduced with a reduced energy intake (80-100 kcal/kg/day). Once a child has stabilised, there is a ‘transition phase’ consisting of either ready to use therapeutic foods (RUTF) with supplemental F75 or alternatively another milk formula known as F100. RUTF is a peanut based, energy dense supplement used to obtain catch-up growth. F100 is a liquid formula with a higher energy density and protein content than F75. The caloric intake is increased daily to a maximum of 130 kcal/kg/day. Finally, ‘Phase 3’ is the recovery phase during which the aim is to achieve catch-up growth with either RUTF or F100.

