Enrolment will occur at the time that F75 milk would normally be started. Details of the study will be communicated to the parents/guardians of potential participants. Prior to seeking informed consent, information on benefits and risks will be provided to parents or carers in their local language and written informed consent sought. In order to ensure patients receive optimal care, to avoid delaying urgent feeding (i.e. as per WHO recommendations to prevent hypoglycaemia), assent for participation will be sought, and then written consent requested after the initial stabilisation. In the rare event that a child for whom assent for participation has been given, but who dies before written consent has been given, data and samples will be used for the study but parents and caregivers will not be asked for written consent at this time of grief. This approach is being successfully used in another study SSC#1778.

Baseline data of prognostic importance will be collected, including vaccination status. A blood sample for haemoglobin and storage of plasma, will be collected at enrolment (up to 5ml, not exceeding 1ml/kg body weight).

*Investigational product*

We will evaluate the effect of a lactose free, reduced carbohydrate F75 compared to standard F75:

1. F75 with 63% of total energy from carbohydrates, including 10% of energy from lactose (standard F75).

2. F75 with 43% of total energy from carbohydrates, without any lactose, and providing the same amount of energy as standard F75 by increased lipid in the form of medium chain triglycerides.

Although increasing energy from lipids to 52% could potentially result in some fat malabsorption leading to steatorrhoea, it will not cause osmotic diarrhoea. Steatorrhoea does not cause severe dehydration and electrolyte imbalances. In the standard RUTF that currently used in severely malnourished children, the energy content provided by lipids is ~60%, which is well tolerated in this patient group.

Standard F75 and reduced carbohydrate F75 will be manufactured to GMP standards by Nutriset®, France who are the current supplier to UNICEF and the Kenyan and Malawian national programmes, and through these channels, to the study hospitals. Protein and micronutrient components will be unchanged and taste is very similar. The study products will be identically packaged, marked ‘for research use only’. Dosing will be as per Kenyan and Malawian recommendations: 130 kcal/kg/day per day, divided into 8 feeds per 24 hours.

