|  | % Energy | | Quantity: g/1000ml | |
| --- | --- | --- | --- | --- |
|  | **Standard F75** | **Modified F75** | **Standard F75** | **Modified F75** |
| Protein | 5.3% | 5.3% | 9.9 | 9.9 |
| Lipid | 31.5% | 51.7% | 26.3 | 43.1 |
| Carbohydrate | 63.2% | 43.0% | 118.5 | 80.6 |
| **Total** | **100%** | **100%** | **154.7** | **133.6** |
|  |  |  |  |  |
| Lactose | 9.9% | 0% | 18.6 | 0 |
| Sucrose | 3.6% | 3.6% | 6.8 | 6.8 |
| Maltodextrin | 50% | 39% | 93.2 | 73.9 |

*Formulations of standard F75 and modified F75*

*Randomisation*

Sequential study numbers will be generated for each site according to a prepared blocked randomisation list of random block sizes before the study begins. Randomisation codes linking allocation to study number will be held by the local safety monitor and chair of the DSMC be opened only in case an individual safety concern or until the database is unlocked. Children will be allocated study numbers sequentially within each site, thus randomly allocating the intervention and maintaining blinding. Group allocation will remain unknown to participants and trial personnel, including the trial-coordinator and principal investigator. Code breaks will be provided to the research team, to be used only in the case of an emergency; 24 hour access will be provided to these code breaks by mobile phone.

*Clinical care*

Children will be managed to the best standard available in each facility, in line with the Kenyan and WHO recommendations. HIV testing by rapid antibody test is routinely offered by the hospitals involved in the trial at admission to all severely malnourished children through ‘provider initiated testing’ according to the current National Guidelines for HIV Testing and Counselling in Kenya (2008) and appropriate follow up tests and referral for care are undertaken according to the results.

*Follow up*

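### The only dose given for the study milk, 130 kcal/kg/day, exceeds the protocol's own stabilisation-phase range of 80-100 kcal/kg/day; 130 ml/kg/day was probably meant

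*Protocol*

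**What the plan says.** Four parts of the protocol bear on the dose.

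- **Section 8(d), Investigational product:** "Dosing will be as per Kenyan and Malawian recommendations: 130 kcal/kg/day per day, divided into 8 feeds per 24 hours". No phase is named, and this is the only numeric dose for the study milk.
- **Section 4, Introduction, on phase 1:** F75 "is introduced with a reduced energy intake (80-100 kcal/kg/day"). On the period after stabilisation: "The caloric intake is increased daily to a maximum of 130 kcal/kg/day".
- **Section 3, Summary:** "Both formulations will be given according to current recommendations regarding frequency of feeding and caloric value". No figure is given.
- **Section 8(d), Enrolment:** "Enrolment will occur at the time that F75 milk would normally be started". The Follow up text adds that a child who is returned to phase 1 goes back on the allocated F75.

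The third criterion for stabilisation, under Outcome measures in section 8(d), is that the child tolerates and finishes the whole F75 volume prescribed.

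**The concern.** Treatment with the study milk begins when F75 begins, which is phase 1. A dose stated for it without qualification therefore applies to phase 1, where the Introduction gives a deliberately reduced intake of 80-100 kcal/kg/day. The printed dose lies above that range and equals the ceiling reserved for children who have already stabilised. A child started at 130 kcal/kg/day would have no room for the daily increase that the Introduction describes.

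Three things are at stake.

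1. **Safety.** The Summary links re-feeding syndrome to "switching from a catabolic state to a high energy diet that consists of predominantly carbohydrates", and the Introduction gives the mechanism. Too high a starting energy intake is the hazard the trial sets out to reduce.
2. **The intervention.** What is being tested is a lower carbohydrate load, and the absolute load depends on the dose as well as on the formula.
3. **The primary endpoint.** The dose determines the volume a child must tolerate to count as stabilised, and that threshold should be clear at three hospitals in two countries.

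**Working it through.** **Inputs.** Doses are from sections 4 and 8(d). Composition per 1000 ml is from the formulations table in section 8(d): protein 9.9 g in both formulas, lipid 26.3 g (standard) and 43.1 g (modified), and the carbohydrate row "Carbohydrate | 63.2% | 43.0% | 118.5 | 80.6". The protocol gives no energy factors, so I assume 4, 9 and 4 kcal/g for protein, lipid and carbohydrate.

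**Step 1: energy density, and a check of the assumed factors.**

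- Standard: 9.9×4 + 26.3×9 + 118.5×4 = 39.6 + 236.7 + 474.0 = 750.3 kcal/L. Shares: 5.3%, 31.5%, 63.2%.
- Modified: 9.9×4 + 43.1×9 + 80.6×4 = 39.6 + 387.9 + 322.4 = 749.9 kcal/L. Shares: 5.3%, 51.7%, 43.0%.

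These shares match the table's printed energy percentages, so the factors are consistent with the protocol. Both formulas contain about 0.75 kcal/ml.

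**Step 2: the printed dose against the phase 1 range.**

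130/100 = 1.30 and 130/80 = 1.625, so the printed dose is 30% above the top of the range and 62.5% above the bottom.

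**Step 3: conversion to volume** (kcal/kg/day ÷ 0.75, then ÷ 8 feeds).

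| Dose | kcal/kg/day | ml/kg/day | ml/kg per feed |
| --- | --- | --- | --- |
| As printed | 130 | 173.3 | 21.7 |
| Phase 1, lower end | 80 | 106.7 | 13.3 |
| Phase 1, upper end | 100 | 133.3 | 16.7 |
| 130 read as ml/kg/day | 97.5 | 130 | 16.25 |

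Read as millilitres, 130 falls inside the range. Varying the factors (lipid 8.8 to 9.3 kcal/g, carbohydrate 3.75 to 4.0 kcal/g) moves 130 ml/kg/day to between 93.0 and 99.2 kcal/kg/day across the two formulas, still inside. Over the same variation the printed dose needs 170.4 to 181.7 ml/kg/day.

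**Step 4: carbohydrate load** (litres/kg/day × g/L).

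| | Standard, g/kg/day | Modified, g/kg/day |
| --- | --- | --- |
| At 130 kcal/kg/day | 0.1733×118.5 = 20.5 | 0.1733×80.6 = 14.0 |
| At 80-100 kcal/kg/day | 12.6 to 15.8 | 8.6 to 10.7 |

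The energy intake at which standard F75 supplies the same carbohydrate as modified F75 at the printed dose is 13.97/118.5 × 750 = 88.4 kcal/kg/day. Modified milk at the printed dose would thus carry as much carbohydrate as standard milk given at an ordinary phase 1 intake.

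**The case against.** The strongest reply is that the two figures have different sources. The Introduction summarises WHO guidance, whereas the dosing sentence cites Kenyan and Malawian recommendations, which are not at hand. National practice could differ, and the Clinical care text, which has children managed "in line with the Kenyan and WHO recommendations", does not show that the two sources give the same dose. It also leaves out Malawi, where 320 of the planned 840 children are expected. This stands to a degree: the document alone cannot settle which figure is wrong. But the protocol nowhere says that the national dose exceeds the range in its Introduction, and the inclusion criteria cite a single reference for the Kenyan and WHO guidelines together.

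The second reply is that harm is hypothetical. Staff are to be trained to WHO recommendations, the governing guideline is named in the same sentence as the dose, and nothing shows that a site would follow the printed unit instead. That also stands. The carbohydrate figures above describe a literal reading, not what sites are expected to do.

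Third, the endpoint refers to whatever volume is prescribed for the child, so it can be applied under either figure. True, but the two readings differ by 21.7 against 16.25 ml/kg per feed, and the protocol should leave no doubt about which applies.

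Finally, both arms receive the same dose. The between-arm comparison is not biased by the error. The sample size does not depend on it either: the planning rate of 50% transitioned by day 5 is observed site data and is not shown to change.

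**Conclusion.** The concern holds. The operative dosing sentence contradicts the protocol's own description of phase 1 feeding by 30% to 62.5%, and nothing in the document reconciles them. Confidence in the contradiction is high, since it needs no outside source. That the intended dose was 130 ml/kg/day (97.5 kcal/kg/day) is an inference. It rests on the assumed energy factors, which reproduce the composition table, and on the fact that 130 fits the phase 1 range only in that unit. The sentence also states its time unit twice, which suggests the units were not carefully checked.

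This is an error to correct because it concerns the study product's dose in unstable children and the volume behind one endpoint criterion. It is not a threat to the validity of the comparison.

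**What to change.** Check the Kenyan and Malawian guidelines and the feed charts at the three sites. If they confirm the slip, change the dosing sentence to: *130 ml/kg/day (about 98 kcal/kg/day), divided into 8 feeds per 24 hours*. If 130 kcal/kg/day is truly intended, say so and justify exceeding the phase 1 range in the Introduction.

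In either case, give the dose in both kcal/kg/day and ml/kg/day, and refer to it in the stabilisation criteria as the volume to be tolerated. The cost is one corrected line, a cross-reference, and a check of the guidelines and feed charts. Sample size and analysis are unaffected.

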Typically, the highest mortality rate is found in the early phases of treatment. Children who fail treatment early often have profuse diarrhoea, signs of circulatory insufficiency which is hard to treat. The most recent reports from Zambia and Kenya note a prevalence of diarrhoea of more than 60% amongst children with SAM and it is associated with increased mortality.[^6^](#_ENREF_6)^,^[^7^](#_ENREF_7) Currently at Kilifi County Hospital and Coast Provincial General Hospital, ~20% of children are given either a diluted or lactose-free milk feed during rehabilitation of SAM (unpublished data), although there are no specific guidelines for this. Diarrhoea may be caused by a viral or bacterial gastroenteritis, sepsis, or may be nutritionally induced (osmotic). There are no routinely available tests to distinguish osmotic from infective or other causes of diarrhoea in hospitals in sub-Saharan Africa. Rotavirus vaccine will be introduced in 2014 and its contribution to diarrhoea amongst children with SAM is unknown.

The proportion of energy derived from carbohydrates in F75 is high. The carbohydrates in F75 milk (as well as F100 and RUTF) consist of a mixture of maltodextrin, sucrose and lactose. Disaccharides such as maltose, lactose or sucrose are normally hydrolysed into monosaccharides by disaccharidases localized at the tip of small intestinal villi. The monosaccharides such as glucose and galactose can then be transported across the apical membrane through Na^+^ dependent glucose transporter, whilst fructose makes use of a facilitative fructose transporter. There is limited information on the intestinal function and intestinal carbohydrate absorption in malnourished children. However, data from Jamaica and South Africa suggest that there is impaired absorption of disaccharides (lactose and sucrose), regardless of the presence or suspicion of gastroenteritis.[^8^](#_ENREF_8)^,^[^9^](#_ENREF_9) Limited histological evidence has shown intestinal atrophy in children with SAM.[^10-12^](#_ENREF_10) These data are consistent with clinical signs of lactose malabsorption found in children with severe malnutrition.[^13^](#_ENREF_13) Recently, evidence of impaired absorption of monosaccharide glucose in children with SAM was reported in Malawi.[^14^](#_ENREF_14)

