**5) Justification**

There are theoretical reasons why carbohydrates in F75 might be associated with the development of diarrhoea and refeeding syndrome in severely malnourished children. However, there are no data from trials to inform the optimal carbohydrate content in therapeutic diets for malnourished children. This trial has the potential to improve treatment guidelines, and thereby the outcomes of malnourished children. Amongst children with SAM who present with, or develop diarrhoea after admission, it is unknown what proportion are due to infective and non-infective causes.

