Children will be examined daily whilst in hospital and clinical status recorded on a standardised proforma (appendix d). A blood sample and stool sample will be taken at day 3 to assess for metabolic effects of refeeding and carbohydrate malabsorption. If children deteriorate during the transition phase or phase 2 and are placed back on phase 1, they will receive the same F75 intervention diet as allocated during the initial treatment. The decision to discharge will be made by the usual clinical team rather than trial personnel. Food supplements and/or nutritional counselling and follow up in the nutritional clinic that are the current standard of care at each institution will also be done at discharge. No study follow up after discharge will be done.

[figure not shown]

*Outcome measures*

*Primary outcome:* the choice of primary outcome is based on the therapeutic purpose of F75, which is to achieve stabilisation and thereby allow a child to progress to feeds with higher protein and energy content to enable catch-up growth.

The primary outcome is stabilisation, defined as having reached the second (transition) phase of treatment. The criteria for stabilisation will be according to WHO guidelines:

Absence of any WHO danger or emergency signs: obstructed breathing, respiratory distress, cyanosis, shock (delayed capillary refill plus fast & weak pulse plus temperature gradient), severe anaemia (Hb<5g/dl), congestive cardiac failure, impaired consciousness, convulsions, severe dehydration, profuse watery diarrhoea, vomits everything, hypothermia.

*and*

If there is oedema at baseline, loss of oedema defined as improving from a severe +++ oedema (severe: generalized bilateral pitting oedema including feet, legs, arms and face) to ++ oedema (moderate: no upper arm or upper leg oedema and no facial oedema or from ++ oedema to + (mild: only feet/ankle oedema) or none;

*and*

Tolerating full prescribed volume of F75 feeds and observed to be completing the feeds.

For analysis, children who die before stabilisation will be classified as ‘not transitioned’.

*Pre-specified secondary outcomes*:

1. Number days with diarrhoea (3 or more loose stools within 24h);
2. Number days requiring rehydration fluids (ReSoMal or IV fluids);
3. Percentage change in weight between admission and day 5;
4. Changes in sodium, potassium, magnesium, calcium, phosphate and albumin between admission and day 3;
5. Faecal electrolytes, pH and fat at day 3;

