6. numbers of episodes of ***new onset*** severe clinical deterioration accompanied by one or more of the following features: shock (fast and weak pulse and limb versus core temperature gradient and capillary refill time>3 seconds), respiratory distress (subcostal chest wall indrawing, hypoxaemia (SaO_2_) or requiring oxygen); impaired consciousness (Blantyre coma score<4) or hypoglycaemia (<3.0 mmol/l);
7. mortality until discharge;
8. time to discharge from hospital in days;
9. total days spent in the stabilization phase, including periods when the child may go back to the stabilization phase during a deterioration;
10. the proportion children with a diarrhoeal pathogen detected, (see laboratory procedures on page 8).
11. Exploratory analysis of plasma and faecal markers of gut inflammation and permeability (see laboratory procedures on page 8).
12. Gut microbiome (see laboratory procedures on page 8).
13. Metabolite profiles in plasma and stool (see laboratory procedures on page 8).

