### (b) Data management/analysis

The trial will use the GCP-compliant Openclinica (<https://openclinica.com/> ) database system, which will be hosted at KWTRP in Kenya. Originally developed for small oncology trials, this system has become the leading open-source clinical data capture system for clinical trials. It allows secure remote data entry online from the sites, provides a real-time reporting system and flagging of inconsistencies and database changes for monitoring. We have used this system for several large clinical trials, which have been programed and maintained by the data manager who will be working on this trial. The trial will be register on clinicaltrials.gov along with pre-specified endpoints. Data cleaning and record verification will be completed and a written analysis plan agreed before the database is un-blinded.

Descriptive statistics on baseline characteristics of the participants in each arm will be provided. Bias will be determined by maintaining a screening log of all potentially eligible participants and those who were excluded or randomized into the two arms. This will be presented as a flow diagram in the final published report according to CONSORT statement guidelines.

The primary outcome will be assessed using a Kaplan-Meier analysis and Cox proportional hazards analysis comparing the rate of stabilisation between arms. Differences between arms in the number of days to stabilisation will be compared using a two tailed Mann-Whitney *U* test. Children who die prior to stabilisation will be included in the primary analysis as ‘not stabilised’. Secondary endpoints with binary outcomes (e.g. overall mortality) will be analysed using contingency tables and a chi squared test. Where adjustment for baseline parameters is required, relative risks will be calculated. For continuous variables and count data (e.g. days receiving rehydration fluids or days with diarrhoea), a suitable general linear model (e.g. linear regression, Poisson regression) will be used. For time to discharge, Kaplan-Meier and Cox proportional hazards analysis will be used. These analyses are conducted on the intention-to-treat principle and are considered the confirmatory analysis. We will conduct tests of heterogeneity of effect, and effect modification for both kwashiorkor and HIV infection, which are considered, *a priori,* to potentially alter the response to F75.

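### The diarrhoea-days outcome pools diarrhoea present at admission with diarrhoea that starts on the trial milk, and no outcome measures new onset

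*Protocol*

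**What the plan says.** The protocol's Outcome measures (section 8, d) Procedures) list as secondary outcome 1 "Number days with diarrhoea (3 or more loose stools within 24h"). The definition has no new-onset limit and does not separate children by their status at admission. Outcome 6 in the same list does make such a restriction: "numbers of episodes of *new onset* severe clinical deterioration". Its listed features are shock, respiratory distress, impaired consciousness and hypoglycaemia, so it does not cover diarrhoea.

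The Justification (section 5) argues that F75 carbohydrate may bring diarrhoea on, and it names two groups itself: "Amongst children with SAM who present with, or develop diarrhoea after admission". The Introduction (section 4) cites outside reports that "note a prevalence of diarrhoea of more than 60% amongst children with SAM".

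Section 9(b) gives the analysis: "For continuous variables and count data (e.g. days receiving rehydration fluids or days with diarrhoea), a suitable general linear model", with linear and Poisson regression as examples. No covariate is named for this outcome. The a priori effect modifiers are kwashiorkor and HIV infection.

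**The concern.** Diarrhoea that began before the first trial feed was not started by either formula, yet its days enter the count in full. One total therefore answers two questions together: whether the milk starts diarrhoea, and whether it prolongs diarrhoea already there. A difference between arms cannot be assigned to either. If the effect lies mainly in onset, days carried in from admission dilute it.

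Admission status is also likely to be a strong predictor of the count and is knowable before randomisation. Leaving it out of the model costs precision whichever way the milk acts. At stake is how well the trial's most direct clinical measure of diarrhoea can speak to its own rationale.

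**Working it through.** The protocol gives no rate, SD or power for outcome 1, so there is no stated figure to reproduce. Only the size, 420 per arm, comes from the document (section 8, c) Sampling).

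**Assumptions, none in the protocol.** A share *a* = 40-60% has diarrhoea at admission, with mean 3.5 days (1 + negative binomial with mean 2.5 and shape 2; variance 2.5 + 2.5²/2 = 5.625; mean square 5.625 + 3.5² = 17.875). A proportion *r* = 30% of the rest develop it, with mean 2.5 days (geometric; variance 3.75; mean square 10).

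**Step 1, mean days per child** = 3.5*a* + 2.5(1 − *a*)*r*.
- *a* = 40%: 1.40 + 0.45 = 1.85; admission diarrhoea supplies 1.40/1.85 = 76%.
- *a* = 60%: 2.10 + 0.30 = 2.40; it supplies 2.10/2.40 = 88%.

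**Step 2, halve new onset (30% to 15%) and change nothing else.**
- *a* = 40%: 1.85 to 1.625, a fall of 12%. Arm variances 5.53 and 5.41; SE = √(10.94/420) = 0.161; z = 0.225/0.161 = 1.39; power 29%.
- *a* = 60%: 2.40 to 2.25, a fall of 6%. Variance in the standard arm = 0.6 × 17.875 + 0.12 × 10 − 2.40² = 6.165, and 6.26 in the other arm; SE = √(12.43/420) = 0.172; z = 0.15/0.172 = 0.87; power 14%.
- New onset among children without admission diarrhoea, 30% v 15%: 252 per arm (*a* = 40%) gives 98% power; 168 per arm (*a* = 60%) gives 91%.

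**Step 3, put admission status in the model.** Variance among children without admission diarrhoea (standard arm) = 0.3 × 10 − 0.75² = 2.44.
- *a* = 40%: within-group variance 0.4 × 5.625 + 0.6 × 2.44 = 3.71, against 5.53 unadjusted: ratio 0.67.
- *a* = 60%: 0.6 × 5.625 + 0.4 × 2.44 = 4.35, against 6.165: ratio 0.71.

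That is a cut of about 30%. Simulated ratios lay at about 0.6-0.8, depending on model and scenario.

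**Step 4, a different effect:** onset × 0.80 (30% to 24%) and admission diarrhoea shortened to 0.85 × 3.5 = 2.975 days.
- *a* = 40%: mean 1.85 to 1.19 + 0.36 = 1.55.
- *a* = 60%: mean 2.40 to 1.785 + 0.24 = 2.025.

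Power by the same formulas (two-sided 0.05):

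| Effect | *a* | Pooled count | Count adjusted for admission status | New-onset proportion |
| --- | --- | --- | --- | --- |
| Onset halved only | 40% | 29% | 43% | 98% |
| Onset halved only | 60% | 14% | 19% | 91% |
| Onset × 0.80, admission duration × 0.85 | 40% | 51% | 67% | 33% |
| Onset × 0.80, admission duration × 0.85 | 60% | 65% | 80% | 24% |

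**Step 5, other inputs.** These are simulations of 3,000 trials per scenario with means of 4 days (admission) and 3 days (new), and new onset halved.
- 60% at admission and new-onset rates of 20/30/50%: pooled power 9/15/35%; new-onset proportion 73/92/99.8%.
- 30% at admission, same rates: pooled 24/43/83%; new-onset proportion 93/99/100%.
- 60% at admission, 30% new onset, and admission diarrhoea also shortened by 10/15/20%: pooled 62/84/96%; new-onset proportion 91-93%.

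**The case against.** **The protocol does not exclude admission status.** A reader might infer that it has decided to compare the count without it. Section 9(b) says only that "a suitable general linear model (e.g. linear regression, Poisson regression) will be used". It also contemplates baseline adjustment, in a sentence about relative risks ("Where adjustment for baseline parameters is required, relative risks will be calculated"), and defers to a written analysis plan agreed before unblinding. Silence on a covariate is not a decision against it. This stands. What the protocol does fix is the list of outcomes, and new-onset diarrhoea is not on it.

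**The milk may act on diarrhoea already present.** The Introduction says disaccharide absorption is impaired "regardless of the presence or suspicion of gastroenteritis". A lactose-free feed could then shorten admission diarrhoea too, and total days would capture that. This also stands. It is the reason to keep the total: a new-onset proportion leaves out every child admitted with diarrhoea, and it has only 24-33% power when the onset effect is modest.

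**The inputs are assumed.** The figure above 60% comes from outside reports and is not described as prevalence at admission. Durations, onset rate and dispersion are not in the protocol. With 30% at admission and a 50% new-onset rate, the pooled count reaches 83% power.

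**Other outcomes bear on mechanism.** Rehydration days, faecal electrolytes, pH and fat, and pathogen detection all contribute, and the primary outcome requires that profuse watery diarrhoea be absent. This limits the weight resting on outcome 1, but none of these measures onset.

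**Conclusion.** The point holds as a cheap and worthwhile improvement to one secondary outcome. Outcome 1 pools two kinds of diarrhoea that the protocol itself distinguishes, no outcome measures onset, and no adjustment for admission diarrhoea is named. The consequences are ambiguity between onset and duration, and lost precision.

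Two stronger readings are not supported. The comparison is not biased, because randomisation balances admission diarrhoea in expectation. Nor does the document show that a real reduction in feed-induced diarrhoea would go unseen. That requires a large share with diarrhoea at admission and no effect of the milk on those children, and the Introduction points away from the second condition.

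On the assumed inputs, power for an onset-only halving is about 15-30% on the pooled count and over 90% on new onset. With a 15% shortening of admission diarrhoea and a 20% reduction in onset, the pooled count reaches 51-65% and the new-onset proportion only 24-33%. Neither measure dominates, so the two belong side by side.

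**What to change.** 1. Keep total days with diarrhoea as outcome 1, and state that its model includes diarrhoea at admission (yes/no). On the assumptions above this cuts the variance of the effect by roughly 20-40%. It recovers only part of the loss if the effect is confined to onset (14% to 19% power at 60% with admission diarrhoea), so the second change is needed as well.
2. Add beside it the proportion with new diarrhoea after the first trial feed among children without diarrhoea at admission, compared between arms.

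Replacing the total by a split would be a trade-off, because the total captures shortening of existing diarrhoea; it should stay.

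Cost: one extra reported secondary result, hence one more test, and the baseline or daily form must record diarrhoea at admission. The forms are not shown, but children are examined daily and baseline prognostic data are already planned. No further patients are needed.
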